### Concealment mechanism {16b}

Participants will be grouped according to their demographic characteristics (age) and physical performance (walking ability) after screening assessment (time 0). Each participant will be assigned a random number, generated in a computer spreadsheet (Excel sheet). Then, randomization will be performed sequentially by three groups taking into account age and physical performance subgroups. To ensure that participants are assessed (initial screening) and randomized by their initial differentiating characteristics (age and physical performance), allocation concealment will be ensured until all baseline measurements are completed.

### Implementation {16c}

The researchers (vascular surgeons and research assistants) will be responsible for the identification, selection, enrollment, and screening assessment of patients. Prior to the formal assessment, the data analyst will generate the allocation sequence and assign participants to groups. Other researchers will evaluate and implement the interventions (not blinded). The data analyst will analyze the data without uncovering the allocation of patients.

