### Participant timeline {13}

Time 0 (t0) will be performed as a screening evaluation to ascertain inclusion criteria. Measurements will take place at time 1 (t1 - baseline assessment), 3 months after t1 (time 2: t2), and 6 months after t1 (time 3: t3). The schedule of enrolment, interventions, and assessments is shown in Fig. 1. Participants’ recruitment has already begun.

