### Recruitment {15}

Three hundred patients with PAD and IC, aged between 50 and 80 years, and with a MWD between 50 and 500 m, will be identified and recruited from the outpatient database of the Angiology & Vascular Surgery Department, Centro Hospitalar Universitário Porto (CHUPorto), Porto, Portugal, by a vascular surgeon member of the team. Eligibility for the study will be tested using clinical medical records and a screening evaluation. The listed participants will be contacted by phone and invited to participate in the study. The invitation will include a brief description of the study and the benefits of participating. For those who show interest in participating, a clinical, physical, and psychological screening assessment will be scheduled at the hospital—time 0 (t0 before allocation). In this assessment (t0), participants will sign a written consent and will be assessed (1 h ±) to determine particular and specific eligibility criteria. If there is an impediment to participation (e.g., COVID-19), the patient will be contacted later.

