## Assignment of interventions: allocation

### Sequence generation {16a}

After the identification of patients through consultation of the outpatient database, the fulfillment of the inclusion criteria in the screening session and the patient’s agreement to participate in the study, a random sequence will be created using a random number allocation software, by a researcher external to the team involved in the execution of this study, in order to guarantee the concealment of the allocation of participants by the different groups. Randomization will be carried out in blocks with four strata and the eligible participants will be randomly assigned to three groups, in blocks of multiples of five, and will be stratified according to (i) age (50 to 65 years old; 66 to 80 years old) and (ii) MWD at the baseline (50 to 275 m; 276 to 500 m). The entire process will be overseen by a researcher who will not be directly involved in the intervention or assessments. This researcher will inform the research team of the final allocation of each participant.

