## Assignment of interventions: blinding

### Who will be blinded {17a}

Participants will be blinded to the group they are assigned to; they will only know that all participants will receive a personalized and self-defined walking plan tailored to each one (a physical exercise prescription to be carried out in the area of residence). The researchers (vascular surgeons and research assistants) responsible for identifying, selecting, enrolling, and screening patients will be blinded to group assignments. A data analyst will generate the allocation sequence and assign participants to groups and will be responsible for data analysis. The researcher who will carry out the psychological intervention, the technician who will carry out the physical assessment, and the computer engineer who will define the route of the walking plan tailored to the patient, on the WalkingPad web platform, will not be blind as to the assignment group because each intervention has its specificity. Thus, this will be a single-blind study, as it will not be possible to blind the patients to the outcome or the researchers who implement and administer the intervention.

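### The protocol does not secure a concealed t1 baseline: patients are assigned before the formal assessment, and the unblinded testing staff have no exception for t1

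*Protocol article*

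**What the plan says.** Five sections of the protocol article bear on the order of events.

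- Recruitment {15} describes the screening visit as "time 0 (t0 before allocation".
- Participant timeline {13} makes baseline a separate, later occasion: "Measurements will take place at time 1 (t1 - baseline assessment), 3 months after t1 (time 2: t2".
- Sequence generation {16a} stratifies by age and by "MWD at the baseline (50 to 275 m; 276 to 500 m" metres. It says that an overseeing researcher passes the allocation to the team, but not when.
- Concealment mechanism {16b} says: "Participants will be grouped according to their demographic characteristics (age) and physical performance (walking ability) after screening assessment (time 0". It ends with the assurance that "allocation concealment will be ensured until all baseline measurements are completed".
- Implementation {16c} says: "Prior to the formal assessment, the data analyst will generate the allocation sequence and assign participants to groups". Its next sentence describes the other researchers, who evaluate patients and deliver the interventions, as not blinded.

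Who will be blinded {17a} lists "the technician who will carry out the physical assessment" among the staff who know the group, without limiting this to any visit. Statistical methods {20a} reports changes in the three walking distances from t1 to t2, t2 to t3 and t1 to t3, and forms change scores by subtracting baseline from the 3- and 6-month values.

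**The concern.** The baseline walking tests should be finished before anyone who runs them can know the arm. Here the text puts assignment ahead of the visit that supplies the baseline, and names the person doing the physical tests as unblinded.

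The tests leave room for influence. Functional distance is by definition the point at which the patient chooses to stop. The treadmill test can end in voluntary exhaustion, and rests are allowed in the 6-minute test. How the pain scale is explained, when pain onset is noted and when a test is ended all pass through the technician. If that person knows the arm at t1, baseline can move differently between arms, and such a movement looks like a treatment effect, or hides one, in every change counted from t1.

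**Working it through.** The protocol gives no figure on this point that could be reproduced. The check consists of ordering the events, testing the concealment sentence against each meaning of baseline, and tracing a baseline shift through the analysis.

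**Order of events**

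1. t0 precedes allocation (Recruitment {15}).
2. Patients are grouped for randomisation after t0 (Concealment mechanism {16b}).
3. Assignment precedes the *formal assessment* (Implementation {16c}). By step 1 this cannot be t0. The retention section {18b} and the Discussion use *formal* for the scheduled study assessments, so t1 is the natural reading, although the term is not defined.
4. t1 is the baseline assessment (Participant timeline {13}).

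The order that results is t0, assignment, t1, t2, t3.

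**What the concealment sentence protects**

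- If baseline there means t1, concealment should last through the t1 tests. Implementation {16c} and Who will be blinded {17a} place assignment earlier and list the testing staff as not blind without excepting t1. As written, the sections conflict.
- If baseline means the t0 screening, the sections agree, but nothing protects t1. This usage does occur: Table 1 describes the cognitive test as a baseline measure within screening, and the concealment sentence itself refers to the initial screening.

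Under neither reading does the text secure a concealed t1.

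**Effect of a shift at t1**

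Let mean t1 MWD in one arm be displaced by d metres relative to the others, with follow-up values unaffected.

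- Raw change: (follow-up mean) − (baseline mean + d) = true change − d. The full d enters the t1-to-t2 and t1-to-t3 contrasts between arms. The t2-to-t3 change does not use t1 and is untouched.
- Baseline-adjusted regression with slope b on baseline: the adjusted arm difference moves by −b × d. With b between 0 and 1 the bias is smaller than d, but it is not removed.

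Statistical methods {20a} sets the minimal clinically important difference at 20 m. With d = 20, the raw change moves by 20 m, the whole of that difference, and the adjusted estimate by b × 20 m. The protocol gives no basis for predicting d, so 20 m is only a yardstick.

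**The case against.** The strongest reply is that assignment and disclosure are different acts. Implementation {16c} says when patients are assigned, not when anyone is told. The analyst could assign after t0, keep the result concealed until t1 is complete as {16b} promises, and only then have the team informed as in {16a}. The technician would then be unblinded only at t2 and t3. This reading is possible. It defeats any claim that the technician is known to be unblinded at t1, which a reader might infer but no section states. It does not remove the gap, because it needs baseline in {16b} to mean t1, a disclosure time that {16a} does not give, and an exception that {17a} does not make.

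Other objections also have force:

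- *Formal assessment* is undefined and the schedule figure is not shown. If the t0 treadmill result is simply carried forward as baseline, treadmill MWD is safe and the point is confined to whatever is measured at t1.
- Both tests are run without encouragement, which limits the technician's influence but does not remove it.
- A reader might infer that patients would decline t1 on learning their arm. Who will be blinded {17a} says participants do not know their group, so the documents do not support this.
- A reader might also see bias in patients whose t1 MWD falls in a different stratum from their t0 value. If MWD is assumed uniform over the 450 m eligibility range and the t0–t1 difference is assumed to have an SD of 40 to 70 m, the share is about 0.80 × 40 / 450 = 7% to 0.80 × 70 / 450 = 12%. Those inputs are not in the protocol. In any case, stratifying on a t0 value measured before allocation is valid even if t1 differs.

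The conflict between {17a} and Procedure for unblinding {17b}, which calls outcome assessors blinded, is firmer on its face. It is a separate matter: resolving it for follow-up would not settle when allocation is disclosed relative to t1.

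**Conclusion.** The point holds as a failure of the text to secure a concealed baseline, not as proof of an unblinded one. The t1 walking tests may be done after assignment by staff who may know the arm, and the one sentence that promises otherwise either conflicts with its neighbours or does not reach t1.

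Any differential shift at t1 would carry one for one into the raw changes from baseline and in proportion to the slope into an adjusted analysis. The likely size of a shift cannot be derived from the protocol.

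The conclusion assumes that *formal assessment* means t1 and that at least some walking tests are performed at t1. Both are the natural reading, but neither can be confirmed without the schedule figure, so confidence is medium. The wording still needs correcting, because the rule that protects the primary baseline should not be left to inference.

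**What to change.** Reconcile Sequence generation {16a}, Concealment mechanism {16b}, Implementation {16c} and Who will be blinded {17a}:

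1. State that allocation is released to the team, including the physical-assessment technician, only after all t1 measurements are completed and entered. Replace the clause in {16c} that ties assignment to the formal assessment accordingly.
2. Name the role that releases it. {16a} has an external researcher create the sequence, while {16c} and {17a} give this to the data analyst.
3. Name the MWD value, t0 or t1, that defines the strata. Either is valid if measured before allocation.
4. Document the order actually used. Trial status expects recruitment to finish on April 30, 2022, and Sample size {14} expects the target by the end of May 2022, so a new rule would reach few patients.
5. For patients whose allocation was disclosed before t1, add a sensitivity analysis with the t0 treadmill MWD as baseline. Eligibility already requires that value. Using t0 for all patients in that analysis would keep one definition of baseline. It covers the other distances only if they were also recorded at t0.

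The cost is wording and record-keeping, with no extra visit or test. The one small downside is that arm-specific materials can be prepared only after t1.

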## Assignment of interventions: blinding

### Who will be blinded {17a}

Participants will be blinded to the group they are assigned to; they will only know that all participants will receive a personalized and self-defined walking plan tailored to each one (a physical exercise prescription to be carried out in the area of residence). The researchers (vascular surgeons and research assistants) responsible for identifying, selecting, enrolling, and screening patients will be blinded to group assignments. A data analyst will generate the allocation sequence and assign participants to groups and will be responsible for data analysis. The researcher who will carry out the psychological intervention, the technician who will carry out the physical assessment, and the computer engineer who will define the route of the walking plan tailored to the patient, on the WalkingPad web platform, will not be blind as to the assignment group because each intervention has its specificity. Thus, this will be a single-blind study, as it will not be possible to blind the patients to the outcome or the researchers who implement and administer the intervention.

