### Trial design {8}

The WalkingPad protocol is a single-center, prospective, three-arm, single-blinded (to patients) randomized controlled, and a superior clinical trial with blocked and stratified random allocation.

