### Intervention description {11a}

#### Active control group: WalkingPad group—PaperWPad group

Active control group (ACG) participants will not receive the smartphone with the WalkingPad app. Participants assigned to this group will receive a 24-week walking program supported by a printed HBET prescription. This prescription consists of a walking plan lasting more than 30 min per session, frequency of at least three sessions per week, and use of near-maximal pain during training as an outcome of claudicating pain. This group will receive an education component on PAD, a behavioral change and motivational intervention, in two face-to-face sessions facilitated by a health psychologist. In addition, participants will receive reinforcement phone calls throughout the 24 week of the study. A self-fulfilling walking logbook will be given to patients to promote self-monitoring. The logbook has the following indicators: date and time, duration of the walk, number, and reasons for stopping, and a question that assesses self-satisfaction after the walk [on a scale from 0 (not at all) to 10 (very satisfied)].

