### Outcomes {12}

#### Primary outcome

The primary endpoint will be the WalkingPad-induced change in PFWD, FWD, and MWD measured using a standardized treadmill test and the 6-min walk test (6MWT). PFWD is defined as the distance walked at the onset of claudication pain. FWD is defined as the distance at which a patient chooses to stop because of the discomfort caused by claudicating pain. MWD is defined as the distance at which claudication pain becomes so intense that the patient is forced to stop.

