### Procedure for unblinding if needed {17b}

The design is open-label with only outcome assessors and data analysts being blinded, so unblinding will not occur.

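### The trial is labelled single-blind to patients, but the three interventions are visibly different and section 17b calls the design open-label, so the patient-dependent outcomes are participant-unblinded

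*Protocol article*

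**What the plan says.** The protocol article describes participant blinding in four places.

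- The Abstract (Methods) calls the trial single-blind without saying who is blinded.
- Trial design {8} names the party: "three-arm, single-blinded (to patients) randomized controlled, and a superior clinical trial".
- Who will be blinded {17a} opens with "Participants will be blinded to the group they are assigned to" and explains what patients are told: "they will only know that all participants will receive a personalized and self-defined walking plan tailored to each one". It closes by keeping the single-blind label while saying that "it will not be possible to blind the patients to the outcome or the researchers who implement and administer the intervention".
- Section 17b, on unblinding, states: "The design is open-label with only outcome assessors and data analysts being blinded".

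On the control arm, Intervention description {11a} says: "Active control group (ACG) participants will not receive the smartphone with the WalkingPad app". These patients get a printed prescription and a logbook instead. Both experimental arms get a smartphone with the app.

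**The concern.** A design label tells the reader which biases the trial guards against. A patient blind would mean that knowledge of the assigned intervention cannot colour what patients report or how hard they try. Most outcomes here are open to exactly that influence. Under Primary outcome, "FWD is defined as the distance at which a patient chooses to stop because of the discomfort caused by claudicating pain", and PFWD is read at the onset of pain that only the patient can report. In the 6MWT the patient sets the pace and may rest. SF-36, VascuQoL-6 and WIQ are questionnaires answered by the patient. The Discussion paragraph of the Abstract intends to read superiority of ExpG2 on the primary and secondary outcomes as evidence that the virtual assistant works. If the blind is only nominal, that reading needs a caveat which the label hides.

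**Working it through.** No arithmetic applies: the point depends on no sample size, variance or error rate. The check sets the statements against each other, and then against the interventions and outcomes.

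**Step 1: are the statements compatible?** Trial design {8} and the opening of 17a say that patients are blinded. Section 17b says that only assessors and analysts are. The word *only* excludes patients, so the two cannot both hold. The close of 17a does not help. Its phrase about not blinding patients to the outcome is unclear: it may mean that patients see their own results, or it may concede that they know their treatment. It cannot be used to support the blind.

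**Step 2: could a patient fail to know which intervention they receive?** From Intervention description {11a} and Strategies to improve adherence {11c}:

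| | ACG | ExpG1 | ExpG2 |
|---|---|---|---|
| Monitoring | paper logbook | smartphone app | smartphone app |
| Behavioural intervention | two psychologist sessions plus calls | two psychologist sessions plus calls | virtual assistant; no in-person or phone contact |
| App support line and instruction book | no | yes | yes |

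Every pair of arms differs in something the patient handles or attends. ACG and ExpG1 differ in the device. ExpG1 and ExpG2 differ in the assistant and in human contact. ACG and ExpG2 differ in both. The intervention received cannot be hidden.

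**Step 3: what can the masking sentence in 17a mean?** Patients are told only of the walking plan common to all. Taken at face value, this withholds the content of the other arms. It limits knowledge of the comparison, but it does not conceal the patient's own intervention.

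**Step 4: which outcomes are exposed?**

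- Patient report: PFWD (pain onset), SF-36, VascuQoL-6, WIQ.
- Patient choice: FWD.
- Patient effort: 6MWT.

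MWD is defined by pain that forces the patient to stop. It is less discretionary, and the point does not rely on it.

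**The case against.** The best defence is that 17a describes real, if partial, masking. If controls are never told that an app exists, they cannot be disappointed at not getting one. That stands as far as it goes: the protocol should be allowed to claim it, if true. It does not make patients blind to their group.

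It can also be said that a diary-versus-app trial can never blind patients to what they receive, and that 17b already says open-label, so the reader is not simply misled. Both are fair. The point does not ask for blinding; it asks for one consistent and accurate description. At present the reader gets mixed signals, and the favourable label is the one in the Abstract and the design statement.

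A reader might infer more than the document supports:

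- *That the bias favours the app arms.* The direction is not documented. ExpG2 loses all personal contact while ACG keeps psychologist sessions and calls, so attention could work the other way. The masking sentence also weakens any argument from being denied a phone.
- *That the bias can be put in metres.* One could multiply an assumed expectation effect by a standard deviation from Statistical methods {20a}, where 81 m and 249 m accompany the two ends of the PFWD range. The protocol supplies no such effect, so the result would only restate the assumption.
- *That ExpG2 versus ExpG1 is a safer contrast because both hold a phone.* Those arms also differ visibly, so the comparison is equally unblinded to participants.
- *That superiority should not be claimed on these outcomes.* That is a debatable preference. Nothing in the document requires it; accurate labelling and a stated limitation are enough.

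**Conclusion.** The point holds as a misstated design property. The protocol article claims a patient blind that its own section 17b denies and that its interventions cannot deliver. Six measures are affected: PFWD, FWD, the 6MWT, SF-36, VascuQoL-6 and WIQ. All comparisons among the three arms on them are participant-unblinded. The size and direction of any bias are unknown from the document. The planned numbers and tests are untouched; what changes is how the results may be described and read. The conclusion assumes only that the interventions are delivered as section 11a describes. It does not assume that patients learn what the other arms receive. It should be corrected, but it does not undermine the feasibility of the trial or its interpretability once it is properly described.

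**What to change.** 1. In the Abstract, Trial design {8} and section 17a, replace the single-blind wording with *open-label to participants*, adding *who are not told the content of the other arms* only if that is true.
2. Reconcile these sections with 17b, so that one statement lists who is and is not blinded. The wording of 17b cannot simply be carried over: it counts outcome assessors as blinded, whereas 17a lists the technician doing the physical assessment as not blind.
3. Clarify or delete the phrase in 17a about blinding patients to the outcome.
4. State that all between-arm comparisons on PFWD, FWD, the 6MWT, SF-36, VascuQoL-6 and WIQ, including ExpG2 versus ExpG1, are participant-unblinded and will be interpreted with that limitation.

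This costs a few sentences and a less favourable design label. It needs no new data, patients, procedures or analyses.

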### Eligibility criteria {10}

Inclusion criteria will be the following: (1) PAD with IC (Fontaine II or Rutherford 1–3) due to atherosclerotic disease, (2) Ankle Brachial Index below 0.9 at rest or below 0.73 after exercise (20% decrease), (3) age range between 50 and 80 years, and (4) MWD in treadmill test between 50 and 500 m.

Exclusion criteria will be the following: (1) asymptomatic PAD; (2) critical ischemia (Fontaine III/IV or Rutherford 4–6); (3) previous lower extremity vascular surgery, angioplasty, or lumbar sympathectomy; (4) any condition other than PAD that limits walking; (5) unstable angina or myocardial infarction diagnosed in the last 6 months; (6) inability to obtain ABI measure due to non-compressible vessels; (7) use of cilostazol and pentoxifylline initiated within 3 months before the investigation; (8) active cancer, renal disease, or liver disease; (9) severe chronic obstructive pulmonary disease (GOLD stage III/IV); (10) severe congestive heart failure (NYHA class III/IV); (11) diagnosis of a psychiatric disease that impairs daily life activities and/or with medical records of decompensation episodes in the last year and/or non-adherence to drug therapy; and (12) cognitive impairment (MMSE ≤ 15 for illiterate patients, 22 for those with 1–11 years of schooling; 27 for > 11 years). The program will be implemented by a research team composed of the following elements: vascular surgeons, a nurse, a health psychologist, a clinical physiologist technician, and computer engineers.

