### Confidentiality {27}

The procedures for storing, processing, and protecting personal data will respect the current General Data Protection Regulation (Regulation (EU) 2016/679), Portuguese Law No. 58/2019 of 8 August. Each participant will be assigned a code (unique identification number) in several databases to ensure data independence. All information about the practice of physical exercise obtained through the mobile app will be stored in an online data system platform. The WalkingPad web platform is accessible to team members and patients. As long as the patient remains in the clinical trial, he accepts that the entire research team has access to the data recorded by the WalkingPad web platform. As for the assessment data, only the principal investigator and the data analyst will have access to the complete dataset, which will be stored in different locations and used for research purposes only. Passwords will be used to ensure the protection and security of data (and participants).

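### Recruiting and screening staff are declared blind to assignments, but other sections tell the research team that includes the recruiting surgeons each allocation and give it access to the app platform

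*Protocol article*

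**What the plan says.** Five statements in the protocol article bear on what recruiters know.

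- **Who recruits.** Implementation {16c}: "The researchers (vascular surgeons and research assistants) will be responsible for the identification, selection, enrollment, and screening assessment of patients".
- **What they are said to know.** Who will be blinded {17a}: these same staff "responsible for identifying, selecting, enrolling, and screening patients will be blinded to group assignments".
- **Who is told allocations.** Sequence generation {16a}: "This researcher will inform the research team of the final allocation of each participant". No team member is excepted.
- **Who is in the team.** Eligibility criteria {10}: "The program will be implemented by a research team composed of the following elements: vascular surgeons, a nurse, a health psychologist", followed by two further roles. Recruitment {15} says that patients are identified and recruited "by a vascular surgeon member of the team".
- **Who sees app data.** Confidentiality {27}: while a patient is in the trial, "he accepts that the entire research team has access to the data recorded by the WalkingPad web platform". The control arm has no app: "Active control group (ACG) participants will not receive the smartphone with the WalkingPad app".

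On the sequence itself, Sequence generation {16a} states that "eligible participants will be randomly assigned to three groups, in blocks of multiples of five", within four strata formed by age and baseline maximal walking distance (MWD). Concealment mechanism {16b} promises concealment until baseline measurements are complete. Procedure for unblinding {17b} describes an open-label design in which only outcome assessors and data analysts are blinded, so recruiters are not on that list.

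**The concern.** Concealing a participant's own allocation until after baseline is not enough in a blocked design. If the people who enrol know the earlier allocations in the current block, they gain information about the next one. Recruitment here leaves room for judgement. A surgeon on the team picks candidates from the outpatient database, the study is presented by telephone, and one exclusion criterion is any condition other than peripheral arterial disease that limits walking. A recruiter who expects a particular arm next could delay, encourage or discourage an enrolment, even without intending to. That is selection bias. An intention-to-treat analysis does not remove it, because it acts before randomisation.

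The blinding statement for recruiters is the safeguard against this, and other sections of the same article undercut it. The point is separate from the blinding of patients, of the technician who performs the walking tests and of the analyst.

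**Working it through.** **Step 1: the texts side by side.** The plan gives no figure to reproduce; the conflict is one of wording.

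| Question | Section | Content |
|---|---|---|
| Are recruiters blind? | {17a} | Yes, surgeons and research assistants |
| Are recruiters blind? | {17b} | Not listed; only outcome assessors and data analysts |
| Who is told each allocation? | {16a} | The research team |
| Are the surgeons in that team? | {10}, {15} | Yes, explicitly |
| Are the research assistants in it? | {16c}, {5d} | Implied, not listed in {10} |
| Who sees the platform? | {27} | The entire research team |
| Whose data are on it? | Intervention description {11a} | The two app arms only |

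For the surgeons, the conflict follows from the text. For the research assistants, it depends on their implied membership.

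**Step 2: which block sizes are possible.** Assume 1:1:1 allocation, which the article does not state. A balanced block must then divide by three. Of the multiples of five, 5, 10, 20 and 25 do not; 15 and 30 do. Write the block size as b = 3m, so m = 5 or 10.

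**Step 3: predictability when the arm is announced, as in {16a}.** Assume also that block size is fixed and known to recruiters, and that they know all earlier allocations in the stratum.

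- Next arm certain (two arms used up): 1/(2m + 1). For m = 5: 1/11 = 9.1%. For m = 10: 1/21 = 4.8%.
- At least one arm ruled out: 2/(m + 1) − 1/(2m + 1). For m = 5: 0.333 − 0.091 = 24.2%. For m = 10: 0.182 − 0.048 = 13.4%.
- Best guess correct (name the arm with most places left), by exact recursion over the places remaining: 49.7% at block 15 and 45.7% at block 30. Chance is 1/3 = 33.3%.

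A simulation of 20,000 blocks per size agrees (9.1%, 24.4% and 49.7%; 4.8%, 13.4% and 45.7%).

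**Step 4: predictability from the platform alone.** Recruiters now know only app or no app for earlier patients.

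- Certain to be app (all control places used): 2/(3(m + 1)). For m = 5: 2/18 = 11.1%.
- Certain to be control (all app places used): 1/(3(2m + 1)). For m = 5: 1/33 = 3.0%. Together 14.1%.
- Best guess of app versus control correct: 71.0% at block 15 and 69.2% at block 30. Always guessing app gives 2/3 = 66.7%, so the gain is 4.3 and 2.5 percentage points.

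This route cannot separate experimental group 1 from experimental group 2.

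**Step 5: the reference case.** If recruiters know no earlier allocation, the best guess is right 33.3% of the time and no assignment is certain, whatever the block size.

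**The case against.** The strongest reply is that the term research team is used loosely. The blinding section is the specific rule. It names the staff who are not blind (the psychological interventionist, the physical-assessment technician and the computer engineer), and {16c} separates recruiters from the unblinded researchers who evaluate and implement. On that reading, {16a} means that only those delivering the intervention are told. This may be what was intended, but the text does not say so: {10} lists the surgeons in the team, {15} calls the recruiting surgeon a member, and {27} says the entire team.

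Several other points stand and limit the finding:

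- The confidentiality clause records a permission. It does not show that recruiters look at the platform, and participants carry codes that would have to be linked to patients.
- A reader might infer that the next assignment can simply be read off. The documents do not support that. Most assignments stay uncertain even under the assumptions above, and no section says that recruiters know the block size or that it is fixed. Hidden or varying sizes would lower the figures.
- A reader might also work with blocks of three or six, which are far more predictable. The stated multiples of five rule them out.
- The MWD stratum is generally not settled when a patient is first telephoned, so prediction is realistic mainly after the screening visit.

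The concealment promise in {16b} does not answer the point. On its natural reading it protects each participant's own allocation until that participant's baseline is done; it does not hide the allocations of earlier participants.

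**Conclusion.** The concern holds as a conflict in the text with a moderate possible effect. The claim that recruiters are blind cannot stand beside {16a}, {10}, {15} and {27} as they are worded; this is explicit for the vascular surgeons and implied for the research assistants. The announcement of each allocation is the main leak. It could raise correct prediction of the next arm from 33% to about 50% at block 15 or 46% at block 30, with about 9% or 5% of assignments certain. Platform access adds only a few points and does not identify experimental group 2, the arm on which the trial's hypothesis turns. All these figures rest on 1:1:1 allocation and a fixed block size known to recruiters, neither of which is stated. They measure opportunity. Nothing in the article shows that enrolment was steered.

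**What to change.** 1. In Sequence generation {16a}, state that each allocation is disclosed only to the staff who need it to deliver that participant's intervention.
2. In Confidentiality {27}, exclude recruiting and screening staff from the WalkingPad platform until the last patient is randomised.
3. State that block sizes are withheld from recruiters.
4. Reconcile {16a}, {17a}, {17b} and {27} so that one list says who is blinded, to what and until when.
5. If access was not or cannot be restricted, withdraw the claim in {17a} that recruiters are blinded, and report who knew the allocations. Recruitment had already begun and was due to close in spring 2022, so this may be the applicable route; it remains useful after recruitment closes.

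The cost is a change of user permissions and a few sentences. The small downside is that recruiting surgeons cannot view app data while recruitment is open.
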